## Abstract

**Background:**

Admission to the neonatal intensive care unit (NICU) may disrupt parent-infant interaction with adverse consequences for infants and their families. Several family-centered care programs promote parent-infant interaction in the NICU; however, all of these retain the premise that health-care professionals should provide most of the infant’s care. Parents play a mainly supportive role in the NICU and continue to feel anxious and unprepared to care for their infant after discharge. In the Family Integrated Care (FICare) model, parents provide all except the most advanced medical care for their infants with support from the medical team. Our hypothesis is that infants whose families complete the FICare program will have greater weight gain and better clinical and parental outcomes compared with infants provided with standard NICU care.

**Methods/Design:**

FICare is being evaluated in a cluster randomized controlled trial among infants born at ≤ 33 weeks’ gestation admitted to 19 Canadian, 6 Australian, and 1 New Zealand tertiary-level NICU. Trial enrollment began in April, 2013, with a target sample size of 675 infants in each arm, to be completed by August, 2015. Participating sites were stratified by country, and by NICU size within Canada, for randomization to either the FICare intervention or control arm. In intervention sites, parents are taught how to provide most of their infant’s care and supported by nursing staff, veteran parents, a program coordinator, and education sessions. In control sites standard NICU care is provided. The primary outcome is infants’ weight gain at 21 days after enrollment, which will be compared between the FICare and control groups using Student’s *t*-test adjusted for site-level clustering, and multi-level hierarchical models accounting for both clustering and potential confounders. Similar analyses will examine secondary outcomes including breastfeeding, clinical outcomes, safety, parental stress and anxiety, and resource use. The trial was designed, is being conducted, and will be reported according to the CONSORT 2010 guidelines for cluster randomized controlled trials.

**Discussion:**

By evaluating the impact of integrating parents into the care of their infant in the NICU, this trial may transform the delivery of neonatal care.

**Trial registration:**

NCT01852695, registered December 19, 2012

## Background

### Background and rationale

In the highly technological environment of the neonatal intensive care unit (NICU), infants are physically, psychologically, and emotionally separated from their parents. Recognition that this experience impedes parent-infant interaction and is detrimental to the infant, led to the development of programs such as family-centered care, kangaroo care, and skin-to-skin care [1–3]. However, these programs are based on the common premise that only NICU professionals with special skills can provide the majority of care for the infant. Parents remain relegated to a supportive role, and some have described themselves as voyeurs who are “allowed” to visit and hold their infants [4, 5]. Many feel anxious and unprepared to care for their infants after discharge [6, 7]. This is in stark contrast to the regular nursery, where care is provided by parents from birth.

In 1979, a shortage of NICU nurses in Estonia prompted Levin [8, 9] to implement a “humane” care model in which parents provide nursing care for the infant (except for respiratory care and administration of intravenous [IV] fluid and medication), while nurses provide teaching and guidance to parents. In a non-randomised, before-after comparison, this model was associated with a 37 % improvement in weight gain in the first 20 days of life [9]. This study contributed to the growing body of evidence suggesting that hospitalized infants may thrive best in a quiet environment, with good nutrition, and consistent love and care from their parents, but without excessive stimulation and handling [6, 10, 11]. As first proposed by Bowlby in 1951 [12], the quality and quantity of the interaction between infants and their parents is particularly important to this concept. During the acute phase of NICU care, a variety of studies have reported that maternal presence, specifically through stimuli provided by voice and breast milk odor, results in more stable physiological responses [13, 14], improved oral feeding [15–18], fewer critical events [13, 19], and shorter length of stay [17, 18] for preterm infants. In the longer term, strong, responsive parent-infant interaction has been associated with improved behavioural outcomes in preterm infants [20–22], a relationship that may be inhibited by poor parental mental well-being [23–26]. As such, encouraging parental presence in the NICU, and providing parents with education and support to reduce their stress levels and improve their knowledge and confidence, is essential to improve preterm infant outcomes.

Building on the evidence from the literature and direct observation of the program in Estonia, we developed the Family Integrated Care (FICare) model specifically for the current Canadian NICU environment, to completely integrate parents into the NICU care team. The principle of FICare is that in the NICU, families should be supported, educated, and empowered to provide as much of their infant’s care as they are able [27, 28]. The FICare program includes a parent education program [29], a nursing education program [30], peer-to-peer support from ‘veteran’ parents [31], and adaptation of the unit policies, procedures, and other infrastructure as necessary, to provide social, psychological, and physical supports that enable greater parent participation.

In a pilot study of the FICare program conducted at Mount Sinai Hospital, Toronto, 31 FICare infants were matched 1:2 with control infants (*n* = 62) based on gender, gestational age (± 2 weeks), birth weight (± 300 grams), age at enrollment, and length of stay following enrollment of ≥ 21 days. The rate of change in weight gain was significantly higher in FICare infants compared with control infants (*p* < 0.05). There was also a significant increase in the rate of breastfeeding at discharge (82.1 vs. 45.5 %, *p* < 0.05). The mean Parental Stress Scale: NICU (PSS:NICU [32]) score for FICare mothers was 3.06 ± 0.12 at enrolment, which decreased significantly to 2.30 ± 0.13 at discharge (*p* < 0.05) compared with control mothers, whose stress scores were not significantly reduced (3.25 ± 0.19 at admission, 2.99 ± 0.2 on discharge, *p* > 0.05). Feedback regarding program implementation from the parents and nurses was very positive [33].

### Hypothesis

The FICare pilot study suggested that the model is feasible and safe in a Canadian healthcare setting, and may decrease parental stress and improve infant weight gain as well as other neonatal outcomes. To evaluate the impact of FICare on neonatal and parental outcomes, we designed and initiated a multi-national, multi-center cluster randomized controlled trial. Our hypothesis is that infants whose families complete the FICare intervention will have improved weight gain and better clinical outcomes compared with infants who received standard care in NICUs randomized to the control arm of the trial.

## Methods/Design

### Trial design

Due to the nature of the intervention, which involves changes to unit-level provision of care and interaction between participants, blinding of participants or NICU staff is not possible. Therefore, to avoid contamination of patients in the control arm, the cluster randomized controlled trial design was selected, in which level 3 NICUs were randomized but the intervention was targeted and the outcomes measured at the individual level. Presently, our prospective multi-centre cluster randomized controlled trial is being conducted at 19 tertiary level Canadian, 6 Australian, and 1 New Zealand NICU. The trial was designed, is being conducted, and will be reported according to the CONSORT 2010 guidelines for cluster randomized controlled trials [34]. Mount Sinai Hospital, where the pilot study of FICare was conducted, was assigned *a priori* to the intervention arm. Randomization was stratified by country, and within Canada was stratified by NICU size according to the number of yearly eligible admissions: < 200 (10 Canadian sites) or ≥ 200 (9 Canadian sites) admissions. Randomization of sites was performed using a random number generator. Enrollment in the trial commenced on 1^st^ April, 2013 and will continue until the required sample size of 675 infants in each arm is reached, which is estimated to occur in August, 2015.

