### Sample size calculation

The proposed sample size of 675 infants in each arm of the trial was estimated for the primary outcome of weight gain at 21 days post-enrollment, as measured by the change in z-score (z-score at Day 21 – z-score at enrollment), using preliminary data from the FICare pilot study available at the time of trial design. These data included 20 infants in the FICare group with mean change in z-scores of 0.58 (standard deviation of 0.57), and 40 matched controls with mean change in z-scores of 0.42 (standard deviation of 0.43). Based on this result (38 % increase in mean z-score change) and Levin’s study [9], we anticipated at least a 25 % increase in mean z-score change in the FICare group. The sample size was estimated assuming the above standard deviation estimates from the preliminary data, and using Kerry’s method [46, 47] for unequal cluster sizes, given that 16 sites (6 large with average size of 315 eligible infants per year, and 10 small with average size of 113 eligible infants per year) had agreed to participate in the trial at that time. The sample size of 675 infants per arm has 80 % power to detect a ≥ 25 % difference (absolute difference of 0.11) in z-score change assuming a significance level of 0.05, intra-cluster correlation coefficient (ICC) of 0.01 [48, 49], and a 10 % drop-out rate.

The estimated sample size is feasible to achieve given that approximately 3200 eligible infants are admitted each year to the 16 sites committed at the time of trial design. We also note that statistical power and the number of eligible infants has been increased by recruitment of additional sites; in total 19 Canadian sites (10 large sites and 9 small sites) and 7 Australian/New Zealand sites (all small) have been randomized and approximately 4300 infants are eligible for enrollment annually.

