### Statistical analysis

The unit of analysis will be the individual infant, and all analyses will be based on the intention to treat principle. The distribution of baseline characteristics in the study population will be summarized at the individual and cluster level within each FICare and control groups, using descriptive statistical methods. The primary outcome of weight gain at 21 days post enrollment, will be compared between the FICare and control groups using Student’s *t*-test adjusted for the inflation factor (or design effect) with a minimum variation weight correction [46, 47] to account for intra-cluster correlation and imbalance of cluster sizes. In addition, a two-level hierarchical linear regression model will examine the primary outcome, accounting for clustering, and potential confounders including patient-level characteristics (birth weight, gestational age, small for gestational age, gender, multiple births, admission illness severity, caesarean section, chorioamnionitis, maternal hypertension or diabetes, maternal education, parity) and NICU-level covariates (NICU size, teaching institution).

Secondary outcomes will be compared between the FICare and control groups using similar methods including the Student’s *t*-test for continuous variables and the Chi-square test for categorical variables adjusted for clustering [50, 51], as well as hierarchical linear or logistic regression models, as appropriate. Furthermore, weight change over time will be examined longitudinally using multivariable multi-level hierarchical models to compare the rate of change in weight gain between infants from the two trial arms.

While we realize that multiple comparisons are a concern when more than one analysis of the data is performed, we are not interested in the joint confidence region for all of our hypotheses at once. Rather, we are interested in them one at a time. Under these conditions, Rothman and Greenland [52, 53] argue that “multiple inference procedures … are irrelevant, inappropriate and wasteful of information” because they produce improperly imprecise single intervals.

Prior to data unmasking and analyses, issues relating to missing data and potential sources of bias will be examined and appropriate correction methods determined.

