### Limitations and feasibility

A cluster randomized trial design was selected to evaluate FICare as it is an organizational and behaviour intervention where blinding of participants or investigators is not possible. Cluster randomized controlled trials are more effective at preventing contamination, but more susceptible to biases than trials randomizing individual subjects [54, 55]. In this trial, possible allocation bias is being minimized by the use of appropriate study design methods for cluster randomization including stratification (sites within each country randomized separately; big and small sites in Canada randomized separately) with randomization performed using a random number generator.

Selection bias may arise due to prospective recruitment of families after randomization of NICU sites, and differences in the nature and process of obtaining informed consent. Study coordinators who recruit families are not blinded to their site’s allocation and families consent to participate in rather than be randomized to the FICare intervention or control protocol. At intervention sites, consent is given to participate in the FICare program and to complete study questionnaires and collect infant data, whereas, at control sites consent is given for questionnaire completion and data collection only. Notably, the inclusion criteria at FICare sites require a time commitment of ≥ 6 h, whereas families at control sites are not specifically asked if they would be able to make the same commitment. As such, participants at intervention sites who commit to FICare may differ from those at the control sites, who do not have to commit to spending extended time in the NICU. For example, families who enroll in FICare may be at a higher socioeconomic level or have greater family support than control families.

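### One of the 26 sites, the pilot hospital, was placed in the FICare arm without randomisation, yet it is described as randomised and kept in the primary comparison

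*Protocol article*

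**What the plan says.** The protocol article's Trial design section places the trial at 26 units: it "is being conducted at 19 tertiary level Canadian, 6 Australian, and 1 New Zealand NICU". One of them was not allocated by chance: "Mount Sinai Hospital, where the pilot study of FICare was conducted, was assigned *a priori* to the intervention arm". The same section then says, without an exception, "Randomization of sites was performed using a random number generator".

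Other sections do not carry the exception through:

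- Abstract, Methods/Design: "Participating sites were stratified by country, and by NICU size within Canada, for randomization to either the FICare intervention or control arm".
- Sample size calculation: "in total 19 Canadian sites (10 large sites and 9 small sites) and 7 Australian/New Zealand sites (all small) have been randomized". That is 19 + 7 = 26, every site in the trial.
- Limitations and feasibility: "possible allocation bias is being minimized by the use of appropriate study design methods for cluster randomization including stratification". The pilot hospital is not mentioned there.
- Statistical analysis: "all analyses will be based on the intention to treat principle". The primary t-test and the hierarchical model are described for the FICare and control groups as a whole, with nothing that sets the pilot hospital apart.

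The Background reports favourable pilot results from this hospital. The section on the provider education programme says that its team drew on pilot experience to train others.

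**The concern.** Randomisation makes the arms comparable in expectation only for the sites that went through it. The pilot hospital could appear only in the FICare arm. If its infants grow differently for reasons unrelated to FICare, such as feeding practice or case mix, nothing in the allocation balances that against control. Adjustment for patient characteristics, NICU size and teaching status need not remove it.

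A second mechanism should be kept apart from this. The site has more experience with FICare than the others. That may enlarge the effect there, which bears on generalisability, but it cannot create an effect if FICare does nothing. Only a pre-existing difference threatens the validity of the test.

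The reporting is also at stake. The trial is to be reported under CONSORT as a cluster randomised trial, and the article contradicts itself on how many clusters were randomised.

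**Working it through.** **1. Site counts.** Trial design: 19 + 6 + 1 = 26 sites, one assigned in advance, which leaves 25 randomised. Sample size calculation: 19 + 7 = 26 randomised. Both cannot be right. The Canadian strata also disagree: Trial design has 10 sites below 200 yearly eligible admissions and 9 at or above, whereas the Sample size calculation has 10 large and 9 small.

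**2. The plan's own sample size.** Inputs from the Sample size calculation: SDs 0.57 and 0.43, difference 0.11 (25% of 0.42 is 0.105), 80% power, alpha 0.05 (two-sided assumed), ICC 0.01, 10% drop-out, and 6 large and 10 small sites with 315 and 113 eligible infants a year. I take 3 large and 5 small sites per arm.

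- Averaged SD = √[(0.57² + 0.43²)/2] = 0.505.
- Unclustered n = 2 × 0.505² × (1.960 + 0.842)² / 0.11² = 331 per arm.
- Design effect with minimum-variance weights, N / Σ[m/(1 + (m − 1) × 0.01)], iterated: 1.887, so N = 624.
- Allowing for drop-out: 624/0.9 = 693.

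With 0.105 and the SD pooled over 20 and 40 infants (0.480), the result is 685. Both are within 3% of the stated 675, so the sample size is not in dispute.

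**3. Weight of the pilot site.** The article gives neither the site's size nor the split of sites between arms. Assumptions: 13 sites per arm (5 large, 8 small), a large pilot site, and 675 × 0.9 = 607.5 evaluable infants per arm, spread in the ratio 315:113.

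- Large site: m = 607.5 × 315/2479 = 77.2, where 2479 = 5 × 315 + 8 × 113. Weight = 77.2/(1 + 76.2 × 0.01) = 43.8.
- Small site: m = 27.7, weight 21.9.
- Arm total = 5 × 43.8 + 8 × 21.9 ≈ 394.
- Pilot site's share of weight = 43.8/394 = 11%. Its share of infants is 77.2/607.5 = 13%. With 13 equal sites the share would be 1/13 = 8%.

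**4. Shift in the contrast.** The between-site SD implied by the plan is √0.01 × 0.505 = 0.05. The excess of this site over other FICare sites is an assumption. The standard error of the contrast is √(2 × 0.505²/394) = 0.036. Type I error is Φ(−1.96 + shift/0.036) + Φ(−1.96 − shift/0.036), and applies if the excess is pre-existing.

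| Assumed excess (z) | Between-site SDs | Shift at 11% weight | Share of 0.11 | Type I error |
|---|---|---|---|---|
| 0.05 | 1 | 0.006 | 5% | 5.3% |
| 0.11 | about 2 | 0.012 | 11% | 6.3% |
| 0.16 | about 3 | 0.018 | 16% | 7.9% |

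**5. Power without the site.** This uses a cluster-level t-test with separate arm SDs. Leaving the site out lowers the FICare effective size from 394 to 350.

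- All 26 sites: SE 0.0360, 24 df, power 83.5% at 0.11 and 80.0% at 0.105.
- 25 sites, infants not replaced: SE = √(0.57²/350 + 0.43²/394) = 0.0374, 23 df, power 80.5% and 76.7%.
- 25 sites, infants replaced (effective size 383): SE 0.0363, power 82.7% and 79.1%.

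**The case against.** The article discloses the assignment openly, and this is one cluster of 26. A unit that has already run FICare could hardly serve as a clean control, and contamination is the stated reason for cluster randomisation. The Statistical analysis section also leaves sources of bias and their correction to a step before unmasking. All of this stands, and it limits the severity. It does not make the allocation random or reconcile the sections that disagree.

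A reader might infer more than the documents support:

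- *That the result is inflated by about a fifth of the target.* This needs the pilot difference of 0.58 − 0.42 = 0.16 to be the site's excess over other FICare sites. The pilot compared FICare with control infants, so 0.16 is an estimate of the treatment effect. As a site excess it would be about three between-site SDs. It also needs the site's raw share of infants, about 15% (315 of 4300/2), where the plan specifies minimum-variance weights. At 11% weight even 0.16 gives 16%.
- *That intention to treat is breached.* It is not: the site was assigned to FICare and is analysed there.
- *That the site was chosen because it delivers FICare well.* The article gives no reason for the assignment.
- *That no analysis without the site is planned.* The article is condensed and the analysis plan is not shown, so this cannot be concluded.

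**Conclusion.** The point holds. The article states that one cluster was not randomised, then counts it as randomised, omits it where allocation bias is discussed, and describes a primary comparison that includes it. Following the text gives a partly non-randomised contrast reported as a randomised one.

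A tilt towards FICare is an inference from the site's role as pilot and training centre. The article gives no figure for standard-care growth at this hospital relative to others, so the difference could run either way. The plausible size is modest: 5 to 16% of the target effect, with type I error of about 5.3 to 7.9% if the excess is pre-existing. This rests on the assumed 13 sites per arm, a large pilot site, the plan's ICC of 0.01 and an assumed excess of 0.05 to 0.16 z. The contradiction in the text depends on none of these. It should be fixed, but it does not undermine the trial.

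**What to change.** Before unmasking, make the comparison of the 25 randomised sites the primary analysis. At minimum, prespecify it beside the 26-site analysis, and label the 26-site result as including one non-randomised site.

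Correct the Abstract, the Sample size calculation and the Limitations and feasibility section to say that 25 of 26 sites were randomised, and name the exception where allocation bias is discussed. Reconcile the numbers of large and small Canadian sites between Trial design and Sample size calculation.

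The cost is wording, one further model run and, if the 25-site analysis is primary, about 3 points of power (83.5% to 80.5% at 0.11). If enrolment at the other FICare sites replaces the infants, the loss is about 1 point.

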### Study participants

Eligible study infants include those who are: i) born at ≤ 33 weeks’ gestation; and ii) on no respiratory support or on low-level respiratory support (i.e., oxygen by cannula or mask, or non-invasive ventilation such as continuous positive airway pressure [CPAP], biphasic CPAP and nasal intermittent positive pressure ventilation). As most infants born at ≤ 33 weeks’ gestation are not discharged home until at least 36 weeks’ postmenstrual age, a minimum “dose” of 3 weeks of in-hospital intervention is ensured. An additional inclusion criterion at the intervention sites is that the primary caregiver parent must commit to spending a minimum of 6 h per day with her/his infant between the hours of 7 am and 8 pm to enable attendance at medical rounds and education sessions.

Infants excluded from the study are those who: i) are receiving palliative care; ii) have a major life-threatening congenital anomaly; iii) have a critical illness and are unlikely to survive; iv) are on a high level of respiratory support (mechanical ventilation, high-frequency oscillatory or jet ventilation, extra-corporeal membrane oxygenation); v) are scheduled for early transfer to another hospital; or vi) have parents with an inability to participate (e.g., health, family, social, or language issues that might inhibit their ability to integrate with the health-care team).

